# Procedures Involved*

- 1. Describe and explain the study design.

[figure not shown]
This project will use a prospective, two-period design, summarized in **Figure 2.** Treatment and outcome measures are unblinded. There is no washout period – due to clinical and insurance standards and validated outcome measures designed to be performed every 6 months. This would impose an unmanageable timeline. To eliminate any potential carryover effects that may occur from SLT+Digital to SLT-only (but are not expected to occur in reverse), we will enroll all children and their parent/caregiver **sequentially** into SLT-only period first, and then intervention period with SLT+Digital. After informed consent is obtained, and completion of the intake and review of inclusion and exclusionary criteria, the child and their parent/caregiver will be sequentially enrolled in: 1) Speech-language therapy alone (SLT-only), **and then** (2) Speech-language therapy with digital storybook intervention (SLT+Digital). The recruitment plan will aim for N=50 subjects.

**Figure 2**

- 1. Provide a description of all research procedures being performed and when they are performed, including procedures being performed to monitor subjects for safety or minimize risks.

Our study will conform to the protocol as approved by our Institutional Review Board (IRB). Upon approval by the NCH IRB, recruitment efforts will begin.

Study materials (e.g., study packets) for all participants will be offered in paper and virtual formats.

**Child and Parent/Caregiver Participants:**

Study staff, audiologists, SLPs, nurses, and physicians, will work together and with the EDW to identify eligible participants based on review of clinic schedules and chart reviews. Recruitment will be done by study coordinators (NCH Behavioral Trials Office, or BTO).

*Participation:*

- After informed consent is obtained, and completion of the intake and review of inclusion and exclusionary criteria, families will be given a **Study Packet** **(Parent/Caregiver)** at the beginning of each intervention period**.** Specific materials will depend on the intervention period (pre-SLT or post-SLT) and may include study information, survey information, clinical recommendations, and training documents (**Study Checklist – Parent/Caregiver**, **HMR Visual Timeline**, **Study** **Review Handout - Caregiver**, **Pre-Trial Parent/Caregiver Survey**, **copy of** **Informed Consent** **Form – Parent/Caregiver** with study/IRB contact information, **American Academy of Pediatrics brochure - “Beyond Screen Time – A Parent’s Guide to Media Use”** sheet, and the **Prescribed Reading Flyer**. The **Hear** **Me Read – User Manual** and link to the **Hear Me Read Training video** will be provided in this packet as well.) Study coordinator will assist with HMR training as needed.
- The child will participate in a **Pre-trial SLP Evaluation** consisting of a battery of clinical measures as part of standard clinical care (ROWPVT-4, CELF-P3) for D/HH children. These are behavioral tests, administered by a SLP to assess a child’s language and communication skills**.** This evaluation will be performed by a treating SLP (SLP_T_) as part of standard care, at a standard therapy visit.
- After **Pre-trial SLP Evaluation**, each child will be enrolled into **SLT-only intervention for 6 months (Intervention Period 1)**, the clinically standard test-retest interval for serial behavioral speech-language and literacy assessments in D/HH children. In-person therapy frequency is determined clinically by SLP_T_ and may range from weekly to every 6-months, but frequency is expected to be the same time period for Intervention Period 1 and Intervention Period 2. All of the sessions in this study will be done as part of standard of care visits. There are no additional data collection in-person research visits, unless necessary to collect survey data or requested by the participating caregiver. The SLT-only intervention period is current standard of clinical care with in-person speech-language therapy with SLP_T_, and written goals provided to parents/caregivers based off of individualized pre-trial evaluation. Standardized reading time will be recommended, and prescribed at 20 min, 3x/week, to try to minimize differences between the treatment groups.
- The parent/caregiver will fill out the brief **Reading Questionnaire** at least monthly during the study, to assess parent/caregiver-reported reading habits. The SLP_T_ may collect this information at each speech therapy session.
- After 6 months of therapy, the clinical standard is for re-evaluation (**Post-SLT-only SLP Evaluation**) with the clinical measures (such as ROWPVT-4, CELF-P3). SLP_T_ will complete re-evaluations at the end of **Intervention Period 1**. A study SLP (SLP_S_), who is not involved in providing therapy as a SLP_T_, will validate the scores provided by the SLP_T_. Scores on the ROWPVT-4 and the CELF-P3 will be collected in the **Therapist - Data collection Form** , built in REDCap. SLP_T_ will record evaluations on a NCHa device connected to NCH’s secured network. Once recorded, video files will be stored on a secured encrypted NCH drive, accessible only to study team members and the SLP_T_. Once the video is uploaded to the NCH server, it will be deleted from the device.
- Parent/caregiver survey (**Post-SLT-only-Parent/Caregiver**) on the therapy experience will be filled out after the intervention period.
- Children are then continued in the next phase of the study (**Intervention Period 2)** with the **SLT+Digital intervention** **for 6 months**. In the SLT+Digital phase, the child will receive in-person therapy in identical fashion as the SLT-only intervention period with a SLP_T,_ and also with the same prescribed reading time. However, the SLP_T_ will now **additionally** assign storybooks through HMR. Difficulties using HMR will be directed to Research Information Solutions and Innovation (RISI) at The Research Institute at NCH who is budgeted for support, along with study coordinator. Contact information will be in the **Hear Me Read Training document.**
- At the conclusion of **Intervention Period 2 (Post-SLT+Digital SLP Evaluation)**, a final assessment battery is completed by the SLP_T_ as part of standard clinical care. Scores on the ROWPVT-4 and the CELF-P3 will be collected in the **Therapist - Data collection Form**, built in REDCap.
- SLP_T_ will record evaluations on an NCH device connected to NCH’s secured network. Once recorded, video files will be stored on a secured encrypted NCH drive, accessible only to study team members and the SLP_T_. Once the video is uploaded to the NCH server, it will be deleted from the device.
- To minimize bias, SLP_S_ will be unaware if the re-evaluation is Post-SLT-only or Post-SLT+Digital, whenever possible.
- As before, a survey (**Post-SLT+Digital -Parent/Caregiver**) on the therapy experience will be filled out by the parent/caregiver after the intervention period.
- Parents/caregivers will additionally fill out **Hear Me Read Feedback-Parent/Caregiver** and questionnaires to provide user feedback on the digital platform.

**Treating SLP Participants:**

*Participation:*

- The SLP_T_ will be provided Study Packet (Treating Therapist), which includes study information, survey information, and training documents(**Study Checklist – Treating Therapist, Study Review Handout - Treating Therapist , Hear Me Read Treating Therapist Manual**, **Reading Questionnaire).** Additionally, the research team will provide SLP_T_ with a study iPad on which they will record speech evaluations. Study coordinator will assist with HMR training as needed.
- They will complete treating SLP surveys (**Post-SLT-only-Treating Therapist**) on the therapy experience after the SLT-only intervention period. One set of surveys will be completed for each participating child.
- They will complete treating therapist survey (**Post-SLT+Digital -Treating Therapist**) on the therapy experience after the SLT+Digital intervention period. One set of surveys will be completed for each participating child.
- They will provide user feedback on the digital platform (**Hear Me Read Feedback-Treating Therapist)**. One set of surveys will be completed for each participating child.

**SMS Messaging:**

This study will use Twilio, a third-party platform that is integrated with REDCap, to:

- Send text messages with survey links to a REDCap form: Twilio will send a text message to the participant. The message will contain a link to a REDCap form. The text message will not include PHI or PII. The text message will provide a link to the secure REDCap platform. The participant will click on the link and be directed to a secure REDCap platform to complete the survey.
- Informational texts to study participants.
  1. Describe Procedures performed to lessen the probability or magnitude of risks.
- Study staff will provide instruction on Hear Me Read and troubleshoot, so therapy time is minimally affected.
- Young children are more susceptible to harms from screen time; in light of American Academy of Pediatrics recommendations, we are not enrolling children under age 2 years of age
- At time of child enrollment, study personnel will say the following safety statement during the consent process:
  - **Screen Time Caution script**: “The amount of child screen time spent in performing study tasks are designed to be in accordance with American Academy of Pediatrics limits on screen time. Please read these information sheets regarding AAP guidelines on safe screen time use and creating a family Media Use Plan.”
- Study packet will include printed screen safety information:
  - American Academy of Pediatrics brochure - **“Beyond Screen Time – A Parent’s Guide to Media Use”**
    - Description from AAP website: Parents/caregivers look to their pediatricians and other professionals when it comes to guidance on kids and screen time. This brochure describes how television and other screens, like computers, smart phones, and tablets, can affect children. The brochure contains age-specific guidelines from infants to teens, based on AAP policy. It includes the advantages and risks for children in this digital age and helps parents/caregivers make using these devices safe and fun for the whole family.

6.4 The source records that will be used to collect data about subjects. (Attach all surveys, scripts, and data collection forms.)

**Study documents below.**

**Data Source Forms (electronic in REDCap, input from iPad or abstracted from EPIC):**

- Therapist - Data Collection Form (All part of standard clinical care):
  - Pre-Trial SLP Evaluation data (ROWPVT-4, CELF-P3)
  - Post-SLT-only SLP Evaluation data (ROWPVT-4, CELF-P3)
  - Post-SLT+Digital SLP Evaluation data (ROWPVT-4, CELF-P3)
- Participating parent/caregiver and treating therapist surveys:
  - Pre-Trial Parent/Caregiver Survey
  - Post-SLT-only – Parent/Caregiver
  - Post-SLT+Digital – Parent/Caregiver
  - Hear Me Read Feedback – Parent/Caregiver
  - Post-SLT-only – Treating Therapist
  - Post-SLT+Digital – Treating Therapist
  - Hear Me Read Feedback – Treating Therapist
  - Reading Questionnaires (Parent/Caregiver)

**Study Packet (Parent/Caregiver) contents:**

- - - - Study Checklist – Parent/Caregiver
      - Study Review Handout – Caregiver
      - Pre-Trial Parent/Caregiver Survey
      - Copy of Informed Consent Form – Parent/Caregiver with study/IRB contact information
      - American Academy of Pediatrics brochure - “Beyond Screen Time – A Parent’s Guide to Media Use”
      - Hear Me Read – User Manual
      - Reading Questionnaires

**Study Packet contents (Treating Therapist):**

- - - - - Study Checklist – Treating Therapist
        - Study Review Handout – Treating Therapist
        - Hear Me Read – Therapist Manual
        - Reading Questionnaires (to ask of parents at each speech therapy visit)

**Recruitment and Incentives documents:**

- Recruitment Script – Parent/Caregiver
- Recruitment Script – Treating Therapist
- Hear Me Read 2021 Recruitment Email/Letter
- Hear Me Read 2021 Recruitment Flyer
- Survey – Email/Text Intro and Link text
- Thank You Letter

**Hear Me Read Training documents:**

- Hear Me Read – Treating Therapist Manual
- Hear Me Read – Parent/Caregiver User Manual

**Patient Medical and Demographic Information:** Obtained from the electronic medical record at NCH (see Section 27)

- - Records from Audiology, Speech-Language Therapy, ENT
  - General Demographics and PHI (see Section 27)
  - Audiologic measures
  - Speech perception
  - Degree of hearing loss
- Mode of communication (oral, total communication, manual/sign language)
- Etiology of hearing loss
- Technology (Hearing aid, cochlear implant, none) and dates of service
  - Maternal level education

6.5 What data will be collected during the study and how that data will be obtained.

Child participant data to be collected includes:

1. **Primary Outcomes:**

- Behavioral measures include age-appropriate behavioral surveys administered by a SLP to assess a child’s language and communication skills, conducted as part of standard clinical care. These consist of verbal or pointing tasks in response to verbal or picture prompts and questions. These are documented in **Therapist - Data collection Form** containing data **Pre-Trial SLP Evaluation, Post- SLT only SLP Evaluation, and Post-SLT+Digital SLP Evaluation** consisting of **(see Figure 1):**
  - Raw Score, Standard Score, Percentile Rank, Age Equivalent, and Growth Scale Values where applicable for the following tests.
    - **Speech and Language Outcomes**
      - Vocabulary
      - [Receptive One Word Picture Vocabulary Test (ROWPVT-4)](https://www.pearsonassessments.com/store/usassessments/en/Store/Professional-Assessments/Speech-%26-Language/Receptive-and-Expressive-One-Word-Picture-Vocabulary-Tests-%7C-Fourth-Edition/p/100000338.html#:~:text=The%20ROWPVT%2D4%20tests%20an,when%20presented%20with%20color%20illustrations.) (ages 2.0-70+), 10-15 min
      - Language
        - [Clinical Evaluation of Language Fundamentals Preschool-3 (CELF P3)](https://www.pearsonassessments.com/store/usassessments/en/Store/Professional-Assessments/Developmental-Early-Childhood/Clinical-Evaluation-of-Language-Fundamentals-Preschool-3/p/100002031.html?tab=product-details) (ages 3.0-6.11), 15-20 min

Subtests:

Word Structure (WS)

Sentence Comprehension (SC)

Expressive Vocabulary (EV)

Following Directions (FD)

Recalling Sentences (RS)

Basic Concepts (BC)

Word Classes (WC)

Indices (composite scores of selected subtests):

CLS (Core Language Score) (Ages 3-6)

Receptive Language Index (RLI) (Ages 3-4)

Receptive Language Index (RLI) (Ages 5-6)

Expressive Language Index (ELI-lan) (Ages 3-6)

- - - **Literacy Outcomes**
      - Emerging Literacy
        - [Clinical Evaluation of Language Fundamentals Preschool-3 (CELF P3)](https://www.pearsonassessments.com/store/usassessments/en/Store/Professional-Assessments/Developmental-Early-Childhood/Clinical-Evaluation-of-Language-Fundamentals-Preschool-3/p/100002031.html?tab=product-details) (ages **4.0**-6.11), 15-20 min

Subtests:

Pre-literacy Rating Scale (PRS)

Phonological Awareness (PA)

Index (composite scores of selected subtests):

Early Literacy Index (composite) (ELI-lit) (Ages 4-6)

1. **Secondary Outcomes:**
   - Measures of the impact on therapy experience, obtained from:

- App measured (see below In-App Metrics)
- **Pre-Trial Parent/Caregiver Survey**
  - **Post-SLT-only – Parent/Caregiver**
  - **Post-SLT+Digital – Parent/Caregiver**
  - **Post-SLT-only – Treating Therapist**
  - **Post-SLT+Digital – Treating Therapist**
  - **Hear Me Read Feedback-Parent/Caregiver**
  - **Hear Me Read Feedback-Treating Therapist**
  - **Reading Questionnaires**
- Book Engagement/book-reading habits, obtained from:
  - App measured (see below In-App Metrics)
- **Pre-Trial Parent/Caregiver Survey**
  - **Post-SLT-only – Parent/Caregiver**
  - **Post-SLT+Digital – Parent/Caregiver**
  - **Post-SLT-only – Treating Therapist**
  - **Post-SLT+Digital – Treating Therapist**
  - **Reading Questionnaires**
- Design and usability of the Hear Me Read app, obtained from:
  - App measured (see below App-Measured Metrics) form Hear Me Read app
  - **Pre-Trial Parent/Caregiver Survey**
  - **Hear Me Read Feedback-Parent/Caregiver**
  - **Hear Me Read Feedback-Treating Therapist**

1. **Patient Medical and Demographic Information:**

- Obtained from the electronic medical record at NCH (see Section 27)
- Records from Audiology, Speech-Language Therapy, ENT
- General Demographics and PHI (see Section 27)
- Audiologic measures
  - Speech perception
  - Degree of hearing loss
- Mode of communication (oral, total communication, manual/sign language)
- Etiology of hearing loss
- Technology (Hearing aid, cochlear implant, none) and dates of service
  - Maternal level education

1. **App-Measured Metrics, from Hear Me Read App**

- # books available
- Lings done?
- Book richness/enhancements:
  - Amount of audio
  - Amount of video
  - # of parsed words in the book
  - # categories and words in categories
  - Lexile score
  - Highlights – word count
  - Highlights – themes/topics
  - Highlights – fiction/nonfiction
  - Highlights – category type (enhanced, etc)
- Time:
  - App launch
  - App close
  - When being used (time of day)
  - Time spent doing narration
  - #times book opened
  - Time in app overall
  - Time spent in book
- What’s being consumed:
  - % of book read (each time)
  - #times any word is clicked in a book per session
    - Audio
    - Visual
  - Which categories are clicked (how many and what)

6.6 If there are plans for long-term follow-up (once all research related procedures are complete), what data will be collected during this period.

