# Study Timelines*

- 1. Describe: The duration of an individual subject’s participation in the study.

Each child is anticipated to participate in 2 separate 6-month intervention periods (Intervention Period #1/SLT-only and Intervention Period #2/SLT+Digital), for a total of 12 months. See **Figure 2**. SLP visits may be either evaluations or therapy sessions and are part of standard care. Evaluations at the start of therapy and in 6 month intervals may take 2-2.5 hours each (such as the **Pre-Trial SLP Evaluation, Post-SLT SLP Evaluation, and Post-SLT + Digital SLP Evaluation)**. In-person therapy frequency is determined by SLP_T_ and may range from monthly to weekly. Duration of therapy sessions are typically 1 hour. All of the sessions in this study will be done as part of standard of care visits. There are no additional research visits, unless necessary to collect survey data or requested by the participating caregiver.

- 1. Describe: The duration anticipated to enroll all study subjects.

Feasibility analysis of local subjects (Section 12) indicates 411 D/HH children were seen in 2019 in the age group we are examining. Of these, 141 children had a speech and language evaluation billed in that year. Our power analysis motivates us to recruit a total of 50 patients. It we account for eligibility, choice of participation, and patient volume, we anticipate approximately **9 months-1 year** to recruit fully.

- 1. Describe: The estimated date for the investigators to complete this study (complete primary analyses)

With rolling recruitment and intervention, expected recruitment, and 1 year treatment period, we anticipate approximately **2-2.5 years from start of study** to completion of primary analysis.

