**Child Eligibility:**

- ***Inclusion:***
  - Children ages 3.0-5.11 years at time of initial assessment and
    - Auditory neuropathy in both ears, or
    - Bilateral Sensorineural or mixed hearing loss at least (PTA≥30dB)
- ***Exclusion:***
  - English not primary language (app is English only at present)
  - standard score CLS >2 SD from normal on CELF-P3

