# Local Number of Subjects

12.1 Indicate the total number of subjects to be accrued locally.

A **power analysis** was performed, based off of Raw Scores with the following rationale: A repeated measures design will evaluate the effect of the intervention within person. In this case, the primary goal of the study is to compare the change across time during SLT therapy alone to the change across time with SLT + Digital. A sample size of 43 achieves 90% power to detect a mean of paired differences of 0.75 with an estimated standard deviation of 1.0 and with a significance level of 0.001 using a two-sided paired t-test.   We plan to enroll 50 children at NCH, as well as a parent/caregiver for each child and the child’s treating SLP.

12.2 If applicable, distinguish between the number of subjects who are expected to be enrolled and screened, and the number of subjects needed to complete the research procedures (i.e., numbers of subjects excluding screen failures.)

We expect approximately 411 unique D/HH children in the age range to be seen by our Hearing Program in 1 year, based on 2019 data. Of these, 141 completed a speech and language evaluation in that year and 270 did not. With prospective attention to scheduling and these volumes, we anticipate screening approximately 250-300 patients to achieve 50 that would enroll.

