# Data Management* and Confidentiality

17.1 Describe the data analysis plan, including any statistical procedures or power analysis.

Raw Score, Standard Score, Percentile Rank, Age Equivalent, and Growth Scale Values for the assessment tests will be measured. Power analysis was based off of Raw Score. A 2-by-2 repeated measures design consists of two groups of subjects, each measured at two time points. In this case, the primary goal of the study is to compare the change across time in group 1 to the change across time in group 2. Sample sizes of 13 in group 1 and 13 in group 2 achieve 92% power to detect a difference in mean changes of 2.0 with a standard deviation of 1.0 at the first time point, a standard deviation of 1.0 at the second time point, and a correlation between measurement pairs of 0.300. The significance level (alpha) is 0.010 using a two-sided, two-sample t-test. To detect a mean 1.5 point difference (all else being equal), we would need **21 patients in each group**. To detect a mean 1 point difference (all else being equal), we calculate we would need 44 patients in each arm.

We plan to analyze Intervention Period 1 (SLT) and Intervention Period 2 (SLT+Digital) together using mixed-effects models to account for differences between interventions 1 and 2. For the primary outcomes, evaluate baseline assessments and compare values between groups using Pearson chi-square tests, t-tests, and Wilcoxon-Mann-Whitney tests. If any imbalance in patient characteristics (e.g. age, frequency of therapy) is detected between groups, the imbalanced characteristics will be adjusted for in multivariable mixed-effects linear regression analyses.

All statistical analyses will be conducted using SAS Enterprise Guide, version 7.15 (SAS Institute Inc). Outcomes are reported for the intention-to-treat population and the also reported for the per protocol population. A 2-sided P < .05 was considered statistically significant.

17.2 Describe the steps that will be taken to secure the data (e.g., training, authorization of access, password protection, encryption, physical controls, certificates of confidentiality, and separation of identifiers and data) during storage, use, and transmission.

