**Confidential Health Information**

1. **Please mark all categories that reflect the nature of health information to be accessed and used as part of this research.**

Demographics (age, gender, educational level)

Diagnosis

Laboratory reports

Radiology reports

Discharge summaries

Procedures/Treatments received

Dates related to course of treatment (admission, surgery, discharge)

Billing information

Names of drugs and/or devices used as part of treatment

Location of treatment

Name of treatment provider

Surgical reports

Other information related to course of treatment

None

1. Please discuss why it is necessary to access and review the health information noted in your response above.

Demographic, audiologic, speech, and other medical information that is volunteered by questionnaire or already readily available in the medical records will be collected for use in this study.

The proposed research is a clinical trial in deaf/hard of hearing children with and their interaction with a software platform. The trial will need to be coordinated and executed across multiple Nationwide Children’s Hospital locations. Aspects of medical history (diagnoses, treatments, use of hearing aid, cochlear implant, sign language, language ability, etc) can inform appropriate use of the technology and analysis of results. Response to content could potentially be age- or gender-sensitive, requiring the collection of basic demographic information such as a Date of Birth and gender. Sufficient information will also be needed to ensure fulfillment of inclusion and exclusion criteria.

3.0 Is the health information to be accessed and reviewed the minimal necessary to achieve the goals of this research?  Yes  No

4.0 Will it be necessary to record information of a sensitive nature?  Yes  No

5.0 Do you plan to obtain a federally-issued Certificate of Confidentiality as a means of protecting the confidentiality of the information collected?  Yes  No

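### Eligibility does not require stable device use or established therapy, and 17.1 defines no per-period variable for either, so in affected children the fixed-order period contrast mixes HMR with those events.

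*Protocol*

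**What the plan says.** The study design text in section 6 places all children in the therapy-only period first and the HMR period second, without washout or a parallel group. Section 12.1 states the goal as comparing change under therapy alone with change under therapy plus HMR within the same child.

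The child criteria are short. Inclusion is "Children ages 3.0-5.11 years at time of initial assessment and" either bilateral auditory neuropathy or "Bilateral Sensorineural or mixed hearing loss at least (PTA≥30dB"). The exclusions are a primary language other than English and "standard score CLS >2 SD from normal on CELF-P3". Nothing refers to device use, time since fitting or activation, or time in therapy.

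Sections 6.4 and 6.5 list "Technology (Hearing aid, cochlear implant, none) and dates of service" among the data abstracted from the medical record, so having no device is a foreseen category. Under Study Timelines, "Evaluations at the start of therapy and in 6 month intervals may take 2-2.5 hours each", and the pre-trial evaluation is one of the examples given. Section 6.2 expects, but does not require, the same therapy frequency in both periods.

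On analysis, the Confidential Health Information part says that aspects of medical history, including hearing aid and implant use, "can inform appropriate use of the technology and analysis of results". Section 17.1 plans mixed-effects models and one adjustment rule: "If any imbalance in patient characteristics (e.g. age, frequency of therapy) is detected between groups", the imbalanced characteristics are added to the regression.

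**The concern.** Each child's first six months is the only control for the next six. That works if nothing relevant except HMR changes between the periods. Starting therapy, or being fitted, activated or moved to another device, is a discrete change in exposure to therapy or access to sound. It is distinct from ordinary developmental growth.

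For a child who begins therapy at the pre-trial evaluation, Period 1 is starting therapy and Period 2 is continuing therapy plus HMR. Any start-up gain enlarges the Period 1 change and masks HMR. A device change at entry acts the same way. For a child whose device changes in Period 2, the gain falls in the HMR period and is credited to HMR.

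The adjustment rule in 17.1 does not deal with this as written. The two groups it compares are the same children in two periods, so a fixed characteristic cannot be imbalanced between them. Only a variable measured separately in each period could differ, and no such device or therapy-start variable is defined. At stake is whether a positive or a null result can be attributed to HMR.

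**Working it through.** **Inputs from the protocol.** Section 12.1: mean paired difference 0.75, SD 1.0, two-sided alpha 0.001, n = 43 for 90% power, planned enrolment 50. Section 17.1: results tested at two-sided P < .05. The protocol thus gives two different alphas, and both are carried below.

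**Inputs assumed.** The share of children with an event, *f*, and the extra gain in the affected period, *J*, in SDs of the paired difference. Neither is in the protocol. Section 12.1's SD of 1.0 is taken as the SD of the difference between the two changes.

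**Step 1: the plan's own figure.** For a two-sided paired t-test with standardised effect 0.75 and alpha 0.001, noncentral t with n − 1 degrees of freedom, power is 89.4% at n = 42 and 90.4% at n = 43. The stated 43 is reproduced. At n = 50 power is 95.7%.

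**Step 2: bias.** Let D be the Period 2 change minus the Period 1 change. If a share *f* gains *J* extra in one period:

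- the mean of D shifts by +*fJ* for a Period 2 event and by −*fJ* for an entry event;
- the SD of D becomes √(1 + *f*(1 − *f*)*J*²).

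Example, *f* = 10%, *J* = 2: shift 0.10 × 2 = 0.20; SD √(1 + 0.09 × 4) = √1.36 = 1.166; noncentrality √50 × 0.20/1.166 = 1.21. With no HMR effect, the rejection rate at alpha .05 is 22%.

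**Step 3: results at n = 50.**

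| *f* | *J* | Shift | SD | False-positive rate, Period 2 events, no HMR effect: alpha .05 / 0.001 | Power, entry events, true effect 0.75: alpha 0.001 / .05 |
|---|---|---|---|---|---|
| none | – | 0 | 1.000 | 5% / 0.1% | 95.7% / above 99% |
| 5% | 1 | 0.05 | 1.023 | 6% / 0.2% | 90% / 99.7% |
| 10% | 1 | 0.10 | 1.044 | 10% / 0.4% | 81% / 99.1% |
| 10% | 2 | 0.20 | 1.166 | 22% / 1.6% | 44.5% / 90.5% |

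These treat D as normal with the inflated SD. A simulation of the actual two-part mixture agreed to about one percentage point for the false-positive rate at alpha .05 and for power at alpha 0.001.

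The alpha decides which error matters. At .05 the exposure is mainly to false positives, and at 0.001 mainly to lost power.

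**Step 4: how large the bias would have to be.** A shift equal to the whole design effect needs *fJ* = 0.75, for example 25% of children at 3 SD (0.25 × 3 = 0.75). At 10% and 1 SD it is 0.10, or 0.10/0.75 = 13% of the design effect.

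**The case against.** Much can be said against pressing this hard.

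- **It may be left to the SAP.** Covariates and sensitivity analyses usually sit there, and no SAP is shown. The absence of a device term is therefore not in itself a fault. What remains is protocol content: the eligibility criteria, the fixed order, and an adjustment rule in 17.1 that is framed for two separate groups.
- **A reader might infer that device data are collected and never used.** The Confidential Health Information text gives them a general analytic purpose. It is fair to say only that no model, covariate or exclusion is attached.
- **A reader might infer that the 17.1 rule could never catch a device change.** Its list of examples is open, and device status coded per period could differ between periods. The rule is loose rather than incapable, because that coding is not defined.
- **A reader might infer many therapy-naive children** from section 12.2: "Of these, 141 completed a speech and language evaluation in that year and 270 did not". That split counts evaluations, not therapy, and section 13.1 also recruits treating therapists outside the hospital. Eligibility is checked against treatment dates and assessment scores, and recruitment letters go to established patients. The phrase about evaluations at the start of therapy sits in a description of visit length and may mean study therapy. New starters are possible, but their number cannot be read from the document.
- **The two kinds of event oppose each other** and may partly cancel. Nothing in the design makes them do so.
- **The root weakness is the fixed order without a concurrent control.** This is one instance of it, but one that data already being collected can partly address.

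**Conclusion.** The point holds in limited form. Children whose device or therapy status changes around entry or during the study are eligible. In those children the period contrast combines HMR with that event, and 17.1 defines no variable to separate them. The direction can go either way and the share affected is unknown.

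The size rests wholly on the assumed *f* and *J*. Over the range shown the shift is 0.05 to 0.20 SD, or 7% to 27% of the 0.75 design effect (0.05/0.75 and 0.20/0.75). That is enough to raise the false-positive rate at .05 from 5% to between 6% and 22%, or to cut power at 0.001 from 96% to between 90% and 44.5%.

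The stronger reading, that the contrast measures these events instead of HMR, is not supported. The effect is a mixture, confined to affected children, and a shift as large as 0.75 needs extreme inputs.

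**What to change.** In section 17.1, replace reliance on the between-group imbalance rule for these factors with three pre-specified items:

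1. From the dates and records already abstracted, derive an indicator for each period of a device fitting, activation or change, and an indicator of therapy newly begun at entry. The investigators set the time window for both before outcome data are examined.
2. Enter device status as a time-varying term in the mixed model.
3. Report a supporting analysis without flagged children beside the main result, with the number flagged.

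The supporting analysis should not be a second hurdle for success. If 15 of 50 children were flagged, 35 would remain, and power for 0.75 at alpha 0.001 would fall from 95.7% to 78.6% before any dropout.

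The cost is a few derived variables, one model term and one extra analysis, with no change to enrolment or care. The main downside is lower precision in the restricted set: 43 children remain only if at most (50 − 43)/50 = 14% are flagged or lost. The model term and the restricted analysis reduce the confounding in flagged children. They do not supply the missing concurrent control.
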